## Abstract

**Background:**

Most interventions for depression have shown small or no effects. ‘Third wave‘ cognitive therapy and mentalization-based therapy have both gained some ground as treatments of psychological problems. No randomised trial has compared the effects of these two interventions for patients with major depression.

**Methods/ design:**

We plan a randomised, parallel group, assessor-blinded superiority clinical trial. During two years we will include 84 consecutive adult participants diagnosed with major depressive disorder. The participants will be randomised to either ‘third wave‘ cognitive therapy versus mentalization-based therapy. The primary outcome will be the Hamilton Rating Scale for Depression at cessation of treatment at 18 weeks. Secondary outcomes will be the proportion of patients with remission, Symptom Checklist 90 Revised, Beck’s Depression Inventory, and The World Health Organisation-Five Well-being Index 1999.

**Discussion:**

Interventions for depression have until now shown relatively small effects. Our trial results will provide knowledge about the effects of two modern psychotherapeutic interventions.

**Trial registration:**

ClinicalTrials: NCT01070134

## Background

### Depression

According to the WHO, major depressive disorder is the second largest healthcare problem worldwide in terms of disability caused by illness [1]. It afflicts an estimated 17% of individuals during their lifetimes at tremendous cost to the individual and society [2,3]. Roughly a third of all depressive disorders take a chronic course [4,5]. Approximately 15% of depressive patients will commit suicide over a 10 to 20 year period [6].

### Antidepressants

Antidepressant medication remains the mainstay in the treatment of depression [7]. However, meta-analyses have shown that most antidepressants presumably only obtain a beneficial effect in severely depressed patients, and even this effect seems to be clinically small [8,9]. As the therapeutic benefits of antidepressants seem to be limited there is an urgent need to identify effective interventions for depression.

### ‘Third wave’ cognitive therapy

Cognitive therapy is one of the most well-known and used psychotherapeutic techniques. Aaron T. Beck originally developed cognitive therapy for depression [10]. Beck believed that critical life events could accentuate hidden negative beliefs, which could generate negative automatic thoughts [10]. These negative thoughts could lead to symptoms of depression, which then could reinforce more negative automatic thoughts [10]. The main goal of the original ‘cognitive model of depression’ is to correct these negative beliefs and thoughts in order to treat the depressive symptoms [10]. One review has questioned if this focus on changing thoughts is an effective element of the cognitive therapy [11]. Our systematic review of randomised clinical trials has shown that classic cognitive therapy versus ‘no intervention’ might be an effective intervention for major depressive disorder. However, the effects of cognitive therapy seem relatively small [12].

During the last two decades modern forms of cognitive therapy have been developed. These techniques are often classified as ‘third wave’ cognitive therapies, including dialectical behaviour therapy (DBT), acceptance and commitment therapy (ACT), schema therapy, mindfulness-based cognitive therapy (MBCT), and metacognitive therapy (MCT) [13]. These therapies have drawn great attention throughout the world, and especially mindfulness has been implemented in numerous different contexts in recent years [14-16]. One systematic review has found that ‘third wave’ cognitive therapy might prevent relapse of depression [17], and preliminary trials indicate that ‘third wave’ cognitive therapy versus ‘no intervention’ or ‘treatment as usual’ is effective for acutely depressed patients [18,19]. ‘Third wave’ cognitive therapies might also be effective interventions for other psychological problems [13,15,20,21]. One trial has shown comparable effects between cognitive therapy and ‘third wave cognitive therapy in non-melancholic depression, but the trial only included 45 participants [22]. Even though evidence is lacking, it seems theoretically possible that the treatment elements of ‘third wave’ cognitive therapy might be more effective than classic cognitive therapy for depressed patients [23]. We have chosen ‘third wave’ cognitive therapy as our experimental intervention because it is practically feasible for us to conduct a trial with this intervention.

### Mentalization-based therapy

In some health-care systems psychodynamic therapy is the most commonly used form of psychotherapy [24]. Mentalization-based therapy is a psychodynamic treatment rooted in attachment and personality theory [25]. It aims to strengthen patients’ capacity to understand their own and others’ mental states in attachment contexts in order to address their difficulties with affect, impulse regulation, and interpersonal functioning [25,26]. Mentalization-based therapy was originally developed to treat borderline personality disorder [27] but is now used to treat a variety of different psychiatric disorders such as depression, eating disorders, substance abuse, and other types of personality disorders [25,26].

Our systematic review of randomised clinical trials has shown that psychodynamic therapy versus ‘no intervention’ might be an effective intervention for major depressive disorder [28], but the effects of mentalization-based therapy versus ‘no intervention’ for major depressive disorder has not been examined in randomised trials [28]. We have chosen mentalization-based therapy as our control intervention because it is practically feasible for us to conduct a trial with this intervention.

### ‘Third wave’ cognitive therapy versus mentalization-based therapy

No randomised clinical trials or systematic reviews have been conducted examining the effects of ‘third wave’ cognitive therapy versus mentalization-based therapy [29].

## Design & methods

We will randomise 84 consecutive patients with major depressive disorder 1:1 to one of two interventions:

1. ‘Third wave’ cognitive therapy, approximately n=42.

2. Mentalization-based therapy, approximately n=42.

The inclusion phase is expected to run for about two years.

### Inclusion

Patients will be referred from general practitioners, practicing specialist physicians, medical departments, and psychiatric departments. Referrals may be denied, either by virtue of the referral papers or via a physician interview. All trial participants will be on sick leave due to psychological illness. To participate in the trial the participant must meet all of the inclusion criteria and none of the exclusion criteria. No special announcement of the project will be made to referrers, so the participants will be similar to patients normally referred to a psychiatric outpatient clinic.

The referrals will be discussed at the patient conference, and relevant patients will be offered a preliminary consultation (collection of master data, which can be used by the therapists during the course of treatment) and a subsequent medical consultation. During the medical consultation relevant patients will be informed of and offered participation in the trial. If the patient agrees to participate in the trial, an appointment will be made for completion of relevant questionnaires. If the patient is included according to the inclusion and exclusion criteria, he or she will be randomised to either ‘third wave’ cognitive therapy versus mentalization-based therapy.

### Inclusion criteria

1. Age from 18 to 65 years.

2. Major depressive disorder (SCID I) [30].

3. Beck’s Depression Inventory (BDI II) > 13 [31].

4. Written informed consent.

### Exclusion criteria

1. Current psychosis, diagnosis of schizophrenia, or schizotypal personality disorder (DSM IV-TR) [32].

2. A significant alcohol or substance abuse (assessed during the preliminary consultations).

3. Initiated or changed medical anti-depressive treatment less than six weeks before randomisation.

4. Pregnancy.

5. No written informed consent.

We have chosen not to include participants over 65 years. This is due to the risk of dementia, which may affect treatment effects. We have chosen BDI > 13 as one of the inclusion criteria to be sure that included participants have significant subjective depressive symptoms. Participants with psychosis, schizophrenia, schizotypal personality disorder, pregnancy, alcohol abuse, and substance abuse are excluded because these groups of participants are traditionally assessed in separate trials.

### Interventions

#### Common to both treatment groups

The intensive treatments will last 18 weeks for each participant. The groups will be ‘slow-open’ (new patients enter the group continually) and will contain a maximum of seven patients. After 18 weeks of intensive treatment every participant will be treated with a follow-up intervention with weekly 1.5-hour sessions of group therapy.

All participants will be offered a communal breakfast twice a week, and group psycho-education for one hour a week. Discussion of treatment plans will be offered after four weeks and after 12 weeks of treatment. The lead clinical consultant, who is not otherwise involved in the trial, will shortly after inclusion offer a consultation regarding psychopharmacological treatment of the psychological problems. The lead clinical consultant will be free to choose any relevant medicine. After the first consultation, medical consultations will be offered by demand of the participant. During the course of treatment, all trial participants with children will be offered participation in a parent support group (four weekly one-hour sessions).

In the absence of one of the therapists (illness, holidays, courses, etc.) the individual therapy will be cancelled. The group therapy will continue, to the extent that this is possible. When participants cancel or do not attend, they will not get compensatory sessions.

### ‘Third wave’ cognitive therapy

Traditional cognitive therapy seeks, in general, to identify irrational thoughts and to ‘correct’ these thoughts [10]. ‘Third wave’ cognitive therapy, and so forth mindfulness (see introduction), is more focused on awareness and acceptance of negative feelings. Our cognitive intervention is primarily based on the principles from mindfulness, so we have chosen to classify this cognitive intervention as ‘third wave’ cognitive therapy [13].

The ‘third wave’ cognitive therapy treatment consists of a weekly individual session (45-50 min.) together with weekly mindfulness-skills training group (1.5 hours).

### The weekly individual session includes

- Introduction of the cognitive model and mindfulness.

- Identification of thoughts, feelings, behaviour, and physical sensations.

- Work on acceptance of feelings and life circumstances.

- Work on assumptions.

- Stress reduction.

- Behavioural experiments and acceptance of difficult feelings.

- Self esteem training.

- Mindfulness training.

- Tools to prevent relapse.

### The weekly mindfulness-skills training group includes

Skills training with teaching of the four basic mindfulness skills ‘FALB’ (training in **F**ocusing, **A**cceptance, **L**abelling techniques, **B**ody awareness) together with self-esteem training and mindful communication. The skills training group will run in a continuous cycle of six sessions. Consequently, participants go through the skills training group’s program three times during the course of the intensive treatment.

For details, please see the manual ‘Third wave’ cognitive therapy - a treatment manual’ for a detailed description of the cognitive intervention [33].

### Mentalization-based therapy

The mentalization-based therapy treatment consists of a weekly individual session (45-50 min.), together with weekly group therapy (1.5 hours).

Mentalising means to understand what lies behind thoughts and activities (e.g., mental states, wishes, needs, goals, and other feelings) [25], and is an active process working both consciously and unconsciously [25]. Mentalization is the process by which we make sense of each other and ourselves. The focus of the mentalization-based therapy is on improving the patient’s ability to mentalise — he or she is trained to mentalise.

### Initial task in mentalization-based therapy

The initial task in mentalization-based therapy is to help the patient to see and learn that her reactions are grounded on something. Feelings and reactions can be understood as a result of what happens in relation to others. Furthermore, the patient is trained in realising that it is not obvious what other people think and feel, and consequently other people cannot know what the patient thinks and feels.

### The five steps in mentalization-based therapy

Mentalization-based therapy has five steps that are repeated a number of times during an intervention period. The *first step* is validation of the patient’s current affect — empathising and supporting the patient. This is followed by clarification of the situation and an elaboration on the patient’s feelings and thoughts; what triggered the feeling; etc. The *fourth step* is ‘basic mentalization’. The patient’s feelings are related to the actual circumstances including other people’s reactions, feelings, wishes etc. The *final step* is to work with interpretation and the transference, including transference interpretations. It is important every step is worked through before going to the next step.

In the first part of an intervention period most time is spend working on step 1-3. Later in an intervention period most time will be spend on step 3-5.

### Therapeutic stance

The therapist must try to demonstrate a ‘mentalising attitude’. The therapist’s attitude must be validating, ‘not-knowing’, and curious questioning the patient about feelings and thoughts. The focus must be on feelings and interpersonal relations. It is of great importance that the therapist identifies when the patient is ‘not-mentalising’, and that the therapist intervenes when this happens. The therapist must assist the patient in regulating the level of the emotions so the patient is able to mentalise; with very strong emotions the patient will not be able to realise what lies behind thoughts and activities, i.e., to mentalise. The therapist must remember not to overestimate the patient’s ability to mentalise, which is a common pitfall. The therapist must help the patient get different perspectives on life events, conflicts, etc.

In mentalization-based therapy the work with the transference process is different from the ordinary psychodynamic way [34]. In mentalization-based therapy it is called ‘mentalising the transference’. ‘Mentalising the transference’ means engaging the patient in reflecting on the relation to the therapist and on the therapist’s mind in the here-and-now. This helps the patient to have ideas of how others se her, by talking about it with the therapist and hearing the therapist’s perspective. In mentalization-based therapy transference is not understood as a repetition of earlier ways of relations, and interpretations based on unconscious processes are not part of the therapy. The counter-transference is managed by the therapists by explicitly telling the patient about the feelings and thoughts the therapeutic process arouse in the therapist. The therapist will always try to present another view and perspective to the patient. In mentalization-based therapy the focus is constantly on ‘mentalising’ interpersonal relations including the relation here-and-now between the patient and the therapist [25,35].

Please see ‘Treatment manual for MBT’ for further details [36].

### Therapists

Each intervention group will have two therapists. The ‘third wave’ cognitive therapy and the mentalization-based therapy therapists will have comparable psychotherapeutic education and experience.

### ‘Third wave’ cognitive therapy therapists

1. The principal clinical investigator (M.D.) is a specialist in general medicine. He has over 10 years of experience in cognitive behavioural therapy and mindfulness and is an approved specialist and supervisor in cognitive behavioural therapy (Danish Psychiatric Association).

2. An occupational therapist with seven years of experience in cognitive behavioural therapy.

### Mentalization-based therapy therapists

1. A mentalization-based therapy licensed psychiatrist with over 20 years of experience with psychodynamic therapy and mentalization-based therapy.

2. A nurse with seven years of experience with psychodynamic therapy and mentalization-based therapy.

### Adherence to treatment manual

All individual sessions will be recorded on an audio recorder and all group sessions will be recorded on video. During the trial an independent research assistant will rate 4 × 10 of the recordings (10 sessions each of: ‘third wave’ cognitive therapy individual therapy, mentalization-based individual therapy, ‘third wave’ cognitive therapy group therapy, and mentalization-based group therapy) to check compliance with the manual. This is done using a checklist and the assessor rates the degree of adherence to the manuals 0-5 (0=no adherence; 5=very high adherence).

### Assessments

Before randomisation: Hamilton Rating Scale for Depression (HDRS) [37], Symptom Checklist 90 Revised (SCL 90-R) [38], Beck’s Depression Inventory (BDI II) [31], World Health Organisation-Five Well-being Index 1999 (WHO 5) [39], Structured Clinical Interviews for DSM-IV Disorders (the depression section of SCID I and SCID II) [30,40], Dimensional Assessment of Personality Pathology-Basic Questionnaire (DAPP-BQ) [41], use of medication, age sex, marital status, and education level.

After 9 weeks of intervention: BDI II WHO 5, use of medication, suicide attempts, and suicides during the intervention period.

After 18 weeks of intervention (end of intensive treatment): HDRS, BDI II, WHO 5, SCL 90-R, use of medication, suicide attempts, and suicides during the intervention period.

After 26 weeks of follow-up treatment: HDRS, SCL 90-R, DAPP-BQ, BDI II, WHO 5, suicide attempts, and suicides during the intervention period.

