#### Other outcome measures

- Adverse events. We will classify adverse events as serious or non-serious. Serious adverse events are defined as any medical occurrence that is life threatening, results in death, or persistent or significant disability, or any medical event, which might jeopardise the patient, or require intervention to prevent it [43]. All other adverse events (that is, any medical occurrence not necessarily having a causal relationship with the treatment, but did, however, cause discontinuation of the treatment) are considered as non-serious.

- Scores on HDRS, BDI, SCL 90-R, WHO 5 after 26 weeks of treatment.

- DAPP-BQ.

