### Blinding

The Hamilton psychologist interviewer will be blinded to the treatment allocation and will be instructed to avoid questions beside the Hamilton interview. All interviewees will be instructed not to mention which treatment they have been allocated to. Therefore, the HDRS has been chosen as the primary outcome. It is not possible to blind neither the therapists nor the participants to treatment allocation. A blinded statistician at The Copenhagen Trial Unit will perform statistical analyses with the two intervention groups coded as ‘A’ and ‘B’.

The lead clinical consultant performing the medical consultations will not be blinded to treatment allocation.

All information given to the participants before filling in every questionnaire will be the same for every participant and will be standardised.

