### Ethical considerations and regulatory approval

There are no immediate ethical problems regarding this trial. Research has not identified any significant adverse effects or risks from either of the compared interventions — and we do not know which is the best intervention. During the trial period any adverse event will be reported. The trial has obtained approval by the Regional Ethics Committee of Zealand (no: SJ-43), and is registered at the Danish Data Protection Agency (no: 2008-58-0020).

Participants will be informed of the trial in writing and verbally, and written informed consent will be obtained from every participant before inclusion. All trial participants may, on request, be permitted access to further information about the project. The individual therapists and the principal investigator will perform this function. No expense allowance is offered to trial participants.

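### Adverse events are a named outcome, but the assessment schedule collects only suicide attempts and suicides, which leaves the harms comparison open to under-capture and to capture that differs by arm

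*Protocol article*

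**What the plan says.** Under Other outcome measures, the Protocol article lists adverse events and states: "We will classify adverse events as serious or non-serious". Serious events cover death, threat to life, lasting or significant disability, and medical events that endanger the patient or call for intervention. Non-serious events are narrower: "any medical occurrence not necessarily having a causal relationship with the treatment, but did, however, cause discontinuation of the treatment".

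Under Ethical considerations and regulatory approval it adds: "During the trial period any adverse event will be reported". It does not say by whom, by what means or when.

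The Assessments section gives the content of each visit. Week 9: "After 9 weeks of intervention: BDI II WHO 5, use of medication, suicide attempts, and suicides during the intervention period". Week 18: "HDRS, BDI II, WHO 5, SCL 90-R, use of medication, suicide attempts, and suicides during the intervention period". The follow-up assessment repeats the rating scales, adds the DAPP-BQ, and again names only suicide attempts and suicides as harms.

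On staff, the Therapists section says: "Each intervention group will have two therapists". The two pairs listed do not overlap, and the principal clinical investigator is one of the pair in the experimental arm. On masking, the Blinding section says: "It is not possible to blind neither the therapists nor the participants to treatment allocation". The same section instructs the blinded Hamilton interviewer not to go beyond the Hamilton interview.

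**The concern.** The trial names a harms outcome with two classes, yet the scheduled visits supply only part of one class. Whatever else is recorded depends on someone happening to learn of an event and passing it on. Two things can then go wrong. Events may be missed in both arms, so that a low count looks like safety. Or one arm's staff may hear of, note and forward events more readily than the other's, so that a difference between arms, or its absence, partly reflects reporting habits. Neither can be repaired at analysis, because the missing information was never collected.

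The primary outcome is protected by a blinded assessor, and the information given before questionnaires is standardised. The article describes no such protection for adverse events beyond suicidal acts.

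**Working it through.** **Step 1. Match each outcome to the schedule.**

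- HDRS at week 18: listed at week 18.
- Remission (HDRS below 8): follows from the same HDRS.
- SCL 90-R, BDI II and WHO 5 at week 18: all listed at week 18.
- Later HDRS, BDI, SCL 90-R and WHO 5 scores: listed at the follow-up assessment.
- DAPP-BQ: listed before randomisation and at the follow-up assessment.
- Adverse events: only suicide attempts and suicides are listed, at week 9, week 18 and follow-up.

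Adverse events are the only outcome that the schedule does not fully supply.

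**Step 2. Compare the definitions with the items.** Of the serious class, the schedule covers suicides and suicide attempts. Other deaths, other life-threatening events, disability and events needing intervention have no item. The non-serious class requires knowing that treatment stopped and that a medical occurrence caused it; neither is scheduled. Medication use (weeks 9 and 18) may hint at an event but does not identify one.

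**Step 3. Ask who could learn of an event outside the schedule.**

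- Hamilton interviewers: blinded, but told to avoid other questions (Blinding).
- Lead clinical consultant: common to both arms and unblinded; offers a consultation shortly after inclusion, then sees participants on demand (Interventions; Blinding).
- Treatment-plan discussions after 4 and 12 weeks: the article does not say who leads them or that harms are asked about.
- Research secretary and primary investigator: check completeness, and invitations are repeated by phone or mail; no harms question is described (Prevention of missing values).
- Therapists: weekly individual and group sessions, unblinded, a separate pair in each arm.

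None of these is named as the collector of adverse events. Regular weekly contact belongs to the therapists.

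**Step 4. Illustrate the mechanism.** The article has no adverse-event figure to reproduce. The only input from it is the arm size, 84 / 2 = 42. The true risk *p* and the capture proportions *c* are assumptions.

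Expected recorded events per arm = 42 × *p* × *c*. With equal true risk, the expected risk ratio is (*p* × *c*A) / (*p* × *c*B) = *c*A / *c*B.

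At *p* = 20%:

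- 90% v 90%: 42 × 0.20 × 0.90 = 7.6 in each arm; ratio 1.00.
- 90% v 70%: 7.6 v 42 × 0.20 × 0.70 = 5.9; ratio 0.90 / 0.70 = 1.29.
- 90% v 50%: 7.6 v 42 × 0.20 × 0.50 = 4.2; ratio 0.90 / 0.50 = 1.80.

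The chance that Fisher's exact test gives p ≤ 0.05 although true risks are equal, for the three capture pairs in that order, is:

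- *p* = 10%: 1.6%, 1.8%, 3.2%.
- *p* = 20%: 2.9%, 4.7%, 11.9%.
- *p* = 30%: 3.0%, 6.5%, 20.4%.

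**Step 5. What equal under-capture costs.** The expected ratio stays at 1, but reassurance weakens. With full capture, 0 events in 42 gives a one-sided 95% upper bound of 1 − 0.05^(1/42) = 6.9%. If only half of events were captured, the same zero would be compatible with a true risk up to 6.9% / 0.50 = 13.8%.

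**The case against.** The strongest reply is that this is an article. Who elicits events, and on what form, is detail commonly left to a full protocol, and continuous reporting during the trial does not contradict a visit schedule. This stands in part: silence on procedure alone would be no finding. But the article does fix a schedule, in detail down to marital status and education level. It includes two harms items and stops there, and those items cannot produce the outcome as defined.

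A second reply is that the definition limits the damage. Non-serious events count only if they ended treatment, which the treating team would know, and suicidal acts are asked about three times in both arms. That reduces the number of events at risk of being missed. It does not establish the cause of stopping, and it leaves other serious events without a question.

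Three stronger readings are tempting, and the article does not support them:

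- *That capture rests on the therapists.* No collector is named, and the lead clinical consultant is available to both arms.
- *That the harms comparison is biased.* Bias in the risk ratio needs capture to differ by arm, and nothing shows that it will.
- *That participants who stop therapy lose their only reporting route.* Prevention of missing values plans at least three invitations, with phone or mail contact, for those who miss an assessment.

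**Conclusion.** The point holds as a gap in the schedule with a risk attached, not as a demonstrated bias. Followed as written, the schedule leaves every adverse event other than a suicidal act to unsystematic capture. It also omits the reason for stopping, on which the non-serious class depends. Unblinded therapists who differ by arm make differential ascertainment plausible. One of them is the principal clinical investigator; whether that is the primary investigator who attends assessments is not stated.

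The size cannot be derived from the document. The ratios of 1.29 and 1.80 simply restate the assumed capture ratios and show the mechanism only. Adverse events are neither a primary nor a secondary outcome, so no efficacy conclusion and no sample size changes. The gap is still worth closing before data are collected.

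**What to change.** Add to the Assessments section, at week 9, week 18 and the follow-up assessment, one short form that is identical in both arms. It should ask about new or worsened medical or psychiatric events, hospital admission, and whether and why treatment was stopped. Give it on paper or through the research secretary, not through a therapist. For participants who stopped or miss the visit, use the phone or mail contact already planned under Prevention of missing values.

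Base the between-arm comparison on all events from any source, with the source flagged. Restricting it to participants' answers would lose deaths and events in non-responders.

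If a fuller document already contains such a form, the Assessments section need only state it.

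The cost is one form at three existing assessments, a small amendment, a few minutes per participant and more events recorded. Participants' own reports remain unblinded, so the form makes the enquiry equal in both arms without removing every source of reporting difference.
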